## Background and rationale

Anorexia nervosa (AN) is a psychiatric disorder included among eating disorders with a reported prevalence in women ranging from 0.5 to 2.2% [1]. Pauci-symptomatic forms of AN (i.e., those in which all the diagnostic criteria for AN are not met or only partially met) are 2 to 10 times more frequent than complete forms of AN and account for up to 60% of the patients treated in specialized centers. AN is often associated with psychiatric comorbidities, such as depression and anxiety [2–4], personality disorders [5] and substance abuse [6]. The cost of eating disorders is considerable, as much from individual, familial, and social viewpoints as from an economic viewpoint [7, 8].

According to main international guidelines, involvement of the family in the treatment of adolescents, by means of family therapy, is the recommended therapeutic option [9–11]. Several familial approaches have been developed and implemented over the last decades, among them the Maudsley family-based treatment [12], which is the most commonly implemented form of family treatment to date, and systemic single-family therapy (SFT), which we use in our health care institutions [13]. These modalities have been widely evaluated (see [14] for a review). However, even if studies show better efficacy than other treatments, a significant number of patients do not respond well to this treatment. Across all studies, remission rates are still under 50% 12 to 18 months after the start of treatment. Some families (patients and/or parents) seem reluctant to accept a single-family therapy project, probably because they fear that their family functioning will be challenged or because of an excessive closeness in the therapeutic or family relationships. And even if it is accepted, the single-family therapy approach can fail, particularly as a result of strong resistance to change, substantial family dysfunctions, or serious individual pathologies.

Moreover, economic considerations motivate clinicians and researchers to develop new treatments or improve existing ones to improve efficacy and cost-effectiveness, notably in helping prevent hospitalization, which dramatically increases costs of treatment.

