### Participants

#### Inclusion criteria

All patients treated in outpatient care or hospitalized for AN in one of the three study sites (Pr. [name]’ unit at Institut Mutualiste Montsouris, Paris; Pr. [name]’s unit at the Maison des Adolescents, Cochin Hospital, Paris; Pr. [name]’s unit in Rouen University Hospital) will be offered participation in the study if they (1) have a Diagnostic and Statistical Manual of Mental Disorders fifth edition (DSM-5) diagnosis of AN or a diagnosis of Eating Disorder Not Otherwise Specified (EDNOS), (2) are aged between 13 to 19 years, (3) have been diagnosed with AN or EDNOS before 19 years old, (4) benefit from a social welfare program, (5) live, and their family lives, in Paris and its suburbs or Rouen or in the vicinity of Rouen.

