### Interventions

After their inclusion in the trial, patients and their families will receive either SFT or MFT. For inpatients, intervention will be proposed after the first half of hospitalization (midway between weight at admission and target weight for discharge). For outpatients, intervention will be proposed when the patient’s clinical situation is stable with no indication for a hospitalization. This methodological choice was based on the fact that the introduction of family therapy before nutrition rehabilitation is not beneficial and could even impede the psychotherapeutic process [41]. Treatment as usual will not be otherwise modified.

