#### Secondary outcomes

Secondary outcomes are as follows:Change from baseline to months 12 and 18 in the overall patient’s clinical outcome (weight outcome, i.e., BMI > 10th percentile, presence of menstruation, GOAS category),Change from baseline to months 12 and 18 in the nature and seriousness of patient’s eating disorder symptoms (EDI-2 and EDDS scores),Change from baseline to months 12 and 18 in the nature and seriousness of patient’s other psychopathological symptoms (HADS, BDI-13, LSAS-CA-SR, MOCI, BVAQ-B, RSES, OSI, and C-SSRS scores),Change from baseline to months 12 and 18 in the nature and seriousness of parents’ psychopathological symptoms (HADS, BDI-13, BVAQ-B, RSES, ECI, EDSIS, and MIV-TIG scores),Change from baseline to months 12 and 18 in the quality of family relationships (FAD, SCORE-15, patients’ LEE scale, and parents’ FQ scores),Change from baseline to months 12 and 18 in the perceived quality of life (EDQOL and SOFAS scores for patients, WHOQOL-Bref, LHS, and CarerQOL-7D scores for parents),Number and duration of hospitalizations after inclusion,Patients’ and parents’ satisfaction (CSQ-8 and ECI scores) regarding the intervention,Cost of treatment between inclusion, 12 months, and 18 months thereafter.

Other measures will be explored as potential moderators or mediators of treatment outcome.

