### Statistics

#### Sample size

One hundred and fifty patients and their parents will be recruited.

Power calculation for the primary endpoint of this study is based on the assumption that MFT is not less effective than SFT if a minimal clinical difference of 0.75 kg/m^2^ in mean change of BMI between baseline and 12 months follow-up cannot be shown between groups. The principal judgement criterion*,*
*i.e*., the variation of BMI 12 months after the beginning of treatment, was established after having reviewed family therapy trials and recent trials on AN, whether in the field of family therapy or in other therapeutic trials ([85]). The non-inferiority margin of 0.75 kg/m^2^ is based on clinical experience and is consistent with the scientific literature. The standard deviation of the BMI variation is estimated at 1.45 [85, 86].

Consequently, we determined the size of the sample for a unilateral Student’s *t* test with a significance of 2.5% and a power of 80% with the non-inferiority margin clinically determined for a minimum BMI difference of 0.75 kg/m^2^, assuming the standard deviation to be 1.45.

This procedure led to a required sample size of 60 patients per group. Assuming that the dropout rate is 20% [86], we calculated a sample size of 75 patients per treatment group.

With a total active file of more than 500 patients in the three study sites, we expect to complete the recruitment of 150 eligible patients in 2 years.

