In order to compare financial costs between SFT and MFT, we will make an inventory of the treatments, and we will use the average cost for each ambulatory appointment (psychiatrist, psychologist, etc.) and the average treatment cost for hospitalization if necessary during follow-up; the sum will determine the total cost of treatment for each patient. Transport costs and other associated costs will not be estimated, as most patients live near the hospital. Costs for the two treatment groups will be compared using Fisher-Pitman’s test.

An analysis of quantitative variables (assessment scores) will be performed in the same way as for the principal criterion using an ANCOVA, with the value of each respective variable at admission, and for the status of treatment at inclusion (ambulatory care or hospitalization), as co-variables. Morgan- Russell GOAS scores (with the three following outcomes: good, intermediate, and poor) will be compared between SFT and MFT, using Cochran-Armitage’s tendency test. A measure of ordinal association (Somers’ *D*) will be calculated with a confidence interval of 95%. Amenorrhea and other qualitative variables will be compared using Fisher’s exact test. Additionally, for the clinical variables assessing outcome, analyses looking for moderators and treatment effect mediators will be carried out.

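### BMI above the 10th percentile, menstruation and GOAS category are listed as change from baseline but tested without the baseline state or the inpatient/outpatient stratum

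*Protocol article*

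**What the plan says.** The first item under Secondary outcomes is a change from baseline to months 12 and 18 in the patient's overall "clinical outcome (weight outcome, i.e., BMI > 10th percentile, presence of menstruation, GOAS category").

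The last paragraph of Statistical methods names the tests. The three GOAS categories (good, intermediate, poor) are compared by a Cochran-Armitage test, with Somers' D and a 95% confidence interval. "Amenorrhea and other qualitative variables will be compared using" Fisher's exact test. No baseline value, stratification or restriction by entry status is attached to either. The same paragraph gives each quantitative score an ANCOVA with its own baseline value and the inpatient/outpatient status as covariates, and the primary BMI analysis is adjusted in the same way. Inpatient/outpatient status is also a randomization stratum.

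Three sections bear on the state at entry:

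- **Inclusion criteria** admit a "diagnosis of AN or a diagnosis of Eating Disorder Not Otherwise Specified (EDNOS"). No BMI ceiling and no amenorrhea requirement is listed.
- **Interventions** says therapy is offered to stable outpatients, and to inpatients once they are "midway between weight at admission and target weight for discharge".
- **Eating disorder symptomatology** defines a good GOAS outcome by weight above the 10th percentile plus menstruation. That is a state, with no element of change.

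**The concern.** The outcome list promises change, while the analysis compares status. A patient who enters above the 10th percentile, or with menses, and stays there counts as a favourable result at month 12 without having changed. The percentages by arm therefore mix attainment with maintenance.

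Two things are at stake. First, the state at entry is probably a strong predictor of the state at month 12. It is recorded at inclusion, and these tests do not use it. Second, the secondary objective asks whether MFT is no worse than SFT on these outcomes. Anything that pulls the arms together makes that conclusion easier to reach, and Statistical methods itself warns, when it justifies a per-protocol analysis, about influences that reduce differences.

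**Working it through.** **The plan's own figure.** Inputs from Sample size: margin 0.75 kg/m2, SD of BMI change 1.45, one-sided 2.5%, power 80%. n = 2 × 1.45² × (1.96 + 0.84)² / 0.75² ≈ 59 per arm by the normal approximation. The noncentral t gives 60 (power 80.2%), and 60 / 0.8 = 75. The figure reproduces and this point does not affect it. The article gives no power for the categorical outcomes; 60 evaluable patients per arm is used below.

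**Share in the state at entry (assumption).** The article gives no baseline BMI distribution. Suppose baseline BMI minus the 10th percentile is normal with mean m from -2.5 to -0.5 and SD s of 1.5 or 2.0. Take the plan's 1.45 as the SD of change, with zero mean change independent of baseline.

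- Above the cut-off at entry: Φ(m/s), from Φ(-2.5/1.5) ≈ 5% to Φ(-0.5/2.0) ≈ 40%.
- Above it at month 12: Φ(m/√(s² + 1.45²)), from Φ(-2.5/2.09) ≈ 12% to Φ(-0.5/2.47) ≈ 42%.
- Crossing upward by variation alone: 8% to 14% (simulated).

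**Size of the contrast.** Let f be the share in the state at entry, k the share of these who keep it, and q the success rate in the rest. The rate in an arm is f·k + (1 - f)·q. If k is equal in both arms, the difference is (1 - f)(q2 - q1). Assume q = 35% vs 60% and k = 100%. Fisher power is exact (two-sided 5%, 60 per arm). The stratified column is a simulated Cochran-Mantel-Haenszel test stratified on entry status. The last column is Fisher's test restricted to patients not in the state at entry.

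| f | SFT vs MFT | Difference (points) | Fisher | Stratified | Fisher, not in state at entry |
|---|---|---|---|---|---|
| 0% | 35.0 vs 60.0 | 25 | 75% | 81% | 75% |
| 10% | 41.5 vs 64.0 | 22.5 | 65% | 75% | 66% |
| 20% | 48.0 vs 68.0 | 20 | 54% | 70% | 63% |
| 30% | 54.5 vs 72.0 | 17.5 | 44% | 63% | 59% |
| 40% | 61.0 vs 76.0 | 15 | 35% | 56% | 46% |
| 60% | 74.0 vs 84.0 | 10 | 20% | 41% | 33% |

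At f = 20%, 0.20/0.48 = 42% of SFT patients in the favourable state at follow-up were already in it at inclusion. With k = 85%, Fisher power is 54% (f = 20%) and 32% (f = 40%), against 64% and 45% stratified.

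**When the contrast does not shrink.** Let MFT also prevent loss of the state, with 60% (SFT) vs 85% (MFT) keeping it and f = 20%. SFT = 0.2 × 0.60 + 0.8 × 0.35 = 40%; MFT = 0.2 × 0.85 + 0.8 × 0.60 = 65%. The difference is again 25 points.

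**Precision from baseline BMI.** This was simulated for the BMI cut-off only, with 60 per arm, a common mean gain of the order of 1.5-2.0 kg/m2 and an arm effect of 1.0 kg/m2.

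- Change independent of baseline: Fisher about 33-50%, logistic regression with baseline BMI about 61-72%.
- Lower-weight patients gain more (assumed correlation of change with baseline -0.5): about 63-76% against 83-90%.
- Type I error is near 5% for both analyses; Fisher is slightly conservative (3-4%).

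These ranges belong to the scenarios run. When mean baseline BMI lies close to the cut-off, both powers can fall below them, with the adjusted model still ahead.

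**The case against.** The stated tests are valid. Allocation is randomized 1:1 and stratified, so entry status is balanced in expectation, and Cochran-Armitage and Fisher compare month-12 status without favouring an arm. Ending treatment in a good state is clinically meaningful whether it was attained or kept. All of this stands.

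A reader might infer more than the article supports:

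- **That patients who never changed are counted as recovered.** The article speaks of a good outcome and a weight outcome, not recovery. Bulimic symptoms can still place a patient in the poor category, so meeting the weight component is not the same as being rated good.
- **That the contrast is necessarily diluted.** This needs patients already in the state to fare alike in both arms. The article presents MFT as a tool against relapse, and if it preserves the state the contrast can persist, as shown above.
- **That most patients enter in the state.** The background remark that pauci-symptomatic forms "account for up to 60% of the patients treated in specialized centers" is not a trial baseline and says nothing about the 10th percentile or menses. The midway-to-target rule fixes when therapy is proposed, and describes patients still short of target weight.

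The power gap also depends on assumptions. Drawing change independently of baseline implies a baseline to month-12 correlation of 1.5/2.09 = 0.72 to 2.0/2.47 = 0.81. For m = -1.5 and s = 1.5, the comparison is 46% vs 72% at zero correlation of change with baseline, 75% vs 88% at -0.5, and 93% vs 98% at -0.7. With SD 2.0 at -0.5 it stays wide (60% vs 85%). At zero correlation, 7-9 points of the gap come from Fisher's conservatism rather than from omitting baseline.

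Finally, covariate detail is often left to an analysis plan, and the visit for these tests is not named. But the article does name the tests, and it gives covariates for the scores in the same paragraph. The mismatch is in its own text.

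**Conclusion.** The point holds as a mismatch between outcome and test, with a loss of precision, on secondary outcomes only. It is not an invalid analysis or a bias toward one arm. No sample size or decision rule rests on these outcomes, and the primary BMI comparison is already adjusted for baseline.

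The size cannot be fixed from the article. In the scenarios run, adjustment for baseline BMI raised power from about 33-50% to 61-72%, or from about 63-76% to 83-90% if lower-weight patients gain more. Where patients already in the state do equally well in both arms, an assumed 25-point effect appears as 20 to 15 points when 20% to 40% enter in that state. That would make the arms look alike under an objective of showing MFT no worse than SFT.

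Two limits remain. Adjustment does not stop a patient near the cut-off from crossing it on a single weighing. Nor does a risk difference standardised over all patients undo the (1 - f) factor; it estimates the same overall contrast more precisely. Percentages by entry status are therefore needed as well.

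**What to change.** In the last paragraph of Statistical methods, make the main analysis of these outcomes baseline-adjusted:

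- **GOAS category:** a proportional-odds model with baseline category (or baseline BMI) and inpatient/outpatient status.
- **BMI above the 10th percentile, and amenorrhea:** logistic regression with the baseline state (or baseline BMI) and inpatient/outpatient status, reported as a standardised risk difference with 95% CI.
- **By entry status, descriptively:** the percentage attaining the state among patients not in it at inclusion, and the percentage keeping it among those who were.
- **Supportive:** Cochran-Armitage with Somers' D, and Fisher's exact test.

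The cost is analysis wording only, because the baseline values are collected at inclusion. The small downside is reliance on a model, with a penalised or exact fit if cells are sparse.

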#### Data collection and management

Data will be transferred to observation files as it is collected, whether it is clinical or para-clinical data. An electronic data capture system will be used for this trial. Data collected from the subjects will be directly captured into an electronic case report form (e-CRF). The investigator will log onto the clinical study website via a unique access code. Transmitted data will be made secure by a client certificate. Once a patient’s data is entered, the investigator will be able to sign and confirm his/her e-CRF. The system will support and validate data entry. Missing and erroneous data (e.g., out-of-range data) will be automatically detected and reported to the investigator for correction. In addition to this computerized data quality control, a manual quality check will be carried out by a clinical research assistant appointed by the trial Sponsor.

Essential research documents that come within the law on biomedical research will be archived by all parties for 15 years after the end of research.

All video recordings required for conducting supervision sessions will be destroyed at the end of the trial.

This trial is registered with the French National Commission for Data Protection and Liberties (CNIL) under Chapter IX of law no. 78-17 of 6 January 1978, modified by law no. 2016-41 of 26 January 2016, regarding the treatment of personal data for the purpose of scientific research in the health field.

The Sponsor has required an authorization for the processing of collected data, the use of patients’ identifying data (social security number, email address, videotaped sessions conducted with the informed consent of patients and parents), and access to the National Health Insurance Information System (SIIRNAM) database for the cost-efficiency analysis.

## Discussion

International guidelines recommend to involve families in the treatment of AN, but current forms of family therapy are not totally satisfying, with a rate of dropouts and treatment failure that remains relatively high. THERAFAMBEST randomized controlled trial aims to compare multi-family therapy (MFT) in a young outpatient setting to systemic single-family therapy (SFT), as it is presently proposed in the study sites.

The first aim is to examine whether the implementation of MFT is at least as efficacious as that of SFT, in terms of BMI, 12 months after the start of treatment. Secondary aims are to provide new evidence comparing MFT to SFT in terms of efficacy, cost, family satisfaction, and clinical outcome, 12 months after the start of treatment and 6 months after the end of treatment.

The MFT approach has been adapted to AN patients and studies show promising results regarding efficacy, satisfaction with treatment, and prevention of relapse. The current model of MFT, as developed by the Maudsley approach [25], involves an intensive rythm of sessions and strong family motivation to engage in treatment. This modality cannot be easily implemented in our global treatment setting. As a consequence, and given the promising effects of MFT in AN, other French teams have developped their own MFT model in an outpatient setting, and preliminary results are encouraging [38]. However, stronger evidence is still needed, notably a comparison of this new form of family treatment in reference to existing ones.

In the same line, the inclusion and exclusion criteria that we have chosen are deliberately broad, to make this trial as naturalistic as possible and to ensure that our sample is representative of the patients we usually follow in our health- care facilities. We expect to define profiles of best responders for each technique. This would enable us to improve therapeutic indications and achieve greater and earlier efficacy, which is predictive of recovery and absence of chronicity.

This trial also presents some challenges we will have to consider. In order to obtain concrete and significant results, we have to recruit 150 patients and their families in a limited timeframe. If projections based on our regular active list of patients in the different study sites make us confident about an effective recruitment, we will consider the option to open a fourth study site in case of difficulties or unexpected delays.

We also wanted to conduct a follow-up evaluation to assess the maintenance of therapeutic results and to have a better evaluation costs in the long term. This will raise the problem of retention. The psychologists and psychiatrists in charge of evaluation are well versed in this problem and have experience in the management of follow-up evaluations of patients and families [86, 95]. Several strategies will be used to maintain the best retention rate possible, such as regular phone calls and communication with the coordinating psychiatrist. A large part of the evaluations will be possible online, with personal access codes, which will enable us to record important information, even if the patient and/or his/her family are not willing to come to the study site for assessment.

A last challenge concerns minimization of therapists’ bias. Indeed, all therapists involved in the trial are trained in both MFT and SFT. We expect to minimize this potential bias by proper training in the use of the therapeutic manuals, regular communication between all therapists, and sessions of supervision.

### Trial status

The trial was registered on ClinicalTrials.gov, NCT03350594, on 22 November 2017; IDRCB number 2016-A00818-43. Recruitment for the trial is ongoing (and started in June 2018). Sessions of MFT and SFT began in September 2018. Recruitment will be completed in September 2021 (approximately).

## Abbreviations

AN: Anorexia nervosa
BMI: Body mass index
ED: Eating disorder
EDNOS: Eating Disorder Not Otherwise Specified
MFT: Multi-family therapy
SFT: Systemic single-family therapy
